##### **4.16.7.1. Laboratory Tests**

In addition to standard laboratory testing per hospital guidelines, other study-specific tests are provided in [Table 3](#). Full human leukocyte antigen-typing (blood) will also be performed.

## **5. TREATMENT OF PATIENTS**

### **5.1. DESCRIPTION OF STUDY DRUG**

#### **5.1.1. Manufacturing of agenT-797**

agenT-797 is a cell therapy consisting of  $\geq 95\%$  allogeneic human unmodified iNKT cells isolated from 1 healthy donor mononuclear cell apheresis unit and expanded ex vivo at a contractual development and manufacturing organization according to current Good Manufacturing Practice (GMP). At the end of the manufacturing process, cells are immediately formulated using CryoStor CS10 containing albumin (human) 25% before aseptic filling into freezing bags. The drug product is stored frozen in the vapor phase of liquid nitrogen ( $\leq -140^{\circ}\text{C}$ ).

#### **5.1.2. Infusion of agenT-797**

After thawing and dilution (see [Section 6.4.1](#)), agenT-797 will be administered as a single intravenous (IV) infusion of allogeneic iNKT cells over 10 to 30 minutes. Patients will be monitored in the clinic for at least 4 hours postinfusion.

In the event of reactions/toxicities during the infusion, the infusion rate may be modified, but the total infusion time should not exceed 60 minutes.

## **5.2. SUPPORTIVE CARE**

Supportive care will be per the Investigator and institutional guidelines. Patients will continue standard of care treatment, as required.

## **5.3. PRIOR AND CONCOMITANT MEDICATION AND THERAPY**

Any medication that is considered necessary for the patient's welfare and will not interfere with agenT-797 (see below), may be given at the discretion of the treating Investigator. All concomitant therapies must be reported in the case report form (CRF) throughout the study.

### **5.3.1. Premedication with agenT-797 Infusion**

Thirty minutes prior to the commencement of the agenT-797 infusion, patients will be given paracetamol (500 to 1000 mg orally) and diphenhydramine (50 mg orally), or IV equivalent, as premedication and/or as per local institutional guidelines.

### **5.3.2. Recording of Concomitant Medication**

Concomitant medications for medically significant AEs should be recorded until the AE has resolved or is considered stable ([Section 8.1.5](#)).

### **5.3.3. Prohibited Medications**

Prohibited medications include the following:

- Any experimental therapy that has not been registered for other indication(s) at the time of agenT-797 dosing
- QT prolonging drugs should be avoided or switched to non-QT altering alternatives, whenever possible

## **5.4. RISKS ASSOCIATED WITH AGENT-797 ADMINISTRATION**

### **5.4.1. Possible Adverse Events Following Treatment with agenT-797 Infusion**

The most common anticipated potential toxicities resulting from treatment with agenT-797 are outlined below. Some of these possible AEs have also been further defined as AESIs in [Section 8.1.3](#).

#### **5.4.1.1. Cytokine Release Syndrome**

CRS is a systemic inflammatory response characterized by a spectrum of severity, ranging from flu-like symptoms (i.e., fever, myalgia, nausea/vomiting), to hypotension, respiratory and renal failure, and uncontrolled coagulopathy. The onset of CRS can typically occur between 24 hours

and 14 days after the completion of T cell administration. Therefore, after agenT-797 infusion, should CRS occur, it should be managed by the Investigator per institutional guidelines.

The American Society for Transplantation and Cellular Therapy (ASTCT) have published consensus guidelines for grading of CRS (Lee 2019). The ASTCT consensus grading guidelines are presented in Table 4 and align with management algorithms developed by Lee and colleagues (Riegler 2019), which are to be used as a guide for the Investigator in the assessment of CRS.

**Table 4: ASTCT CRS Consensus Grading**

| Parameter          | Grade 1                               | Grade 2                                                  | Grade 3                                                                                       | Grade 4                                                                                |
|--------------------|---------------------------------------|----------------------------------------------------------|-----------------------------------------------------------------------------------------------|----------------------------------------------------------------------------------------|
| Fever*      | Temperature $\geq 38^{\circ}\text{C}$ | Temperature $\geq 38^{\circ}\text{C}$                    | Temperature $\geq 38^{\circ}\text{C}$                                                         | Temperature $\geq 38^{\circ}\text{C}$                                                  |
|                    |                                       | With                                              |                                                                                               |                                                                                        |
| Hypotension | None                                  | Not requiring vasopressors                               | Requiring a vasopressor with or without vasopressin                                           | Requiring multiple vasopressors (excluding vasopressin)                                |
|                    |                                       | And/or†                                |                                                                                               |                                                                                        |
| Hypoxia     | None                                  | Requiring low-flow nasal cannula ‡ or blow-by | Requiring high-flow nasal cannula, ‡ facemask, nonrebreather mask, or Venturi mask | Requiring positive pressure (e.g., CPAP, BiPAP, intubation and mechanical ventilation) |

From Lee 2019.

Abbreviations: ASTCT: American Society for Transplantation and Cellular Therapy; BiPAP: bilevel positive airway pressure; CPAP: continuous positive airway pressure; CRS: cytokine release syndrome; NCI-CTCAE: National Cancer Institute Common Terminology Criteria for Adverse Events.

Organ toxicities associated with CRS may be graded according to NCI-CTCAE v5.0 but they do not influence CRS grading.

\* Fever is defined as temperature  $\geq 38^{\circ}\text{C}$  not attributable to any other cause. In patients who have CRS then receive antipyretic or anti-cytokine therapy such as tocilizumab or steroids, fever is no longer required to grade subsequent CRS severity. In this case, CRS grading is driven by hypotension and/or hypoxia.

† CRS grade is determined by the more severe event: hypotension or hypoxia not attributable to any other cause. For example, a patient with temperature of  $39.5^{\circ}\text{C}$ , hypotension requiring 1 vasopressor, and hypoxia requiring low-flow nasal cannula is classified as Grade 3 CRS.

‡ Low-flow nasal cannula is defined as oxygen delivered at  $\leq 6$  L/min. Low flow also includes blow-by oxygen delivery, sometimes used in pediatrics. High-flow nasal cannula is defined as oxygen delivered at  $> 6$  L/min.

Further, ensure at least 3 vials of tocilizumab, or other anti-IL-6 agents, or current standard treatment regimens are available:

- Administration of tocilizumab 8 mg/kg IV over 1 hour (not to exceed 800 mg) or other anti-IL-6 agents or current standard of care treatment. Repeat tocilizumab or other anti-IL-6 agents or current standard of care treatment every 8 hours as needed if not responsive to IV fluids or increasing supplemental oxygen. Limit to a maximum of 3 doses in a 24-hour period with a maximum total of 4 doses.

## **5.5. TREATMENT COMPLIANCE**

Patients who have enrolled in the study are hospitalized ([Section 4.7.1](#)). Patients who are administered agenT-797 will have treatment recorded in the CRF and Investigators will follow all guidance for study drug management ([Section 6](#)).

## **5.6. RANDOMIZATION AND BLINDING**

This is an open-label study without randomization or blinding of data.

# **6. STUDY DRUG MATERIALS AND MANAGEMENT**

## **6.1. STUDY DRUG**

The investigational medicinal product, agenT-797, is provided formulated with albumin (human) 25% and CryoStor CS10 before aseptic filling into Saint Gobin freezing bags of 2 sizes (20F containing 15 mL, and 62F containing 50 mL) at a concentration of  $2.5 \times 10^7$  cells/mL ([Section 5.1.1](#)).

## **6.2. STUDY DRUG PACKAGING AND LABELING**

Packaging, labeling and release of the finished investigational medicinal product will be in accordance with applicable local regulatory requirements and applicable GMP guidelines.

All study drugs must be kept in a secure place under appropriate storage conditions. The Sponsor or its representatives must be granted access on reasonable request to check drug storage, dispensing procedures, and accountability records. Please see Pharmacy Manual for additional details.

## **6.3. STUDY DRUG STORAGE**

Bulk agenT-797 cells will be cryopreserved and stored in the vapor phase of a liquid nitrogen tank ( $\leq -140^\circ\text{C}$ ). agenT-797 cells for administration will be evaluated against preset release criteria. agenT-797 cells must remain frozen until the patient is ready for treatment to ensure viable allogeneic iNKT cells are administered to the patient. agenT-797 bags must be protected from light.

## **6.4. STUDY DRUG PREPARATION**

### **6.4.1. Thawing of the Infusion Bag and Dilution**

Do not thaw the investigational product until it is ready to be used. Once agenT-797 has been thawed, it will be diluted with Plasma-Lyte A in a 1 to 1 ratio. Once thawed and diluted, it should be infused within 30 to 60 minutes. Details on thawing of agenT-797 are provided in the Pharmacy Manual.

## **6.5. ADMINISTRATION**

Details are provided in the Pharmacy Manual.

## **6.6. STUDY DRUG ACCOUNTABILITY AND DISPOSAL**

The Investigator is responsible to maintain accurate records of study drug shipment receipts from the manufacturer including patient dispensing, product destruction, and documentation of adequate storage of study drug while at the site. Local biosafety guidelines should be followed for unused medicinal product or waste material disposal. Refer to the Pharmacy Manual.

## **7. STUDY ASSESSMENTS**

Please see the Schedule of Assessments provided in [Table 3](#) for details and the timing of each clinical assessment and/or procedure.

## **8. ADVERSE AND SERIOUS ADVERSE EVENTS**

### **8.1. DEFINITIONS**

#### **8.1.1. Adverse Event**

An AE is defined in the International Council for Harmonisation (ICH) Good Clinical Practice (GCP) guideline as “any untoward medical occurrence in a patient or clinical investigation patient administered a pharmacological product and that does not necessarily have a causal relationship with this treatment.”

This includes:

- An undesirable medical condition, which can be symptoms, signs, or the abnormal results of a laboratory investigation.
- An event that is part of infection with SARS-CoV-2 or influenza and is captured in the study as a clinical activity measure, which does not need to be recorded as an AE.
- Any deterioration of the disease under study and associated symptoms or findings, which should not be regarded as an AE as far as the deterioration can be anticipated.

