| 
 
To assess safety and tolerability of agenT-797 infusion
 
                                                                                                                                                                    | 
 
Number and severity of adverse events (AEs) and dose-limiting toxicities (DLTs) at evaluated dose levels
 
                                                                                                                                                                                                                                                                                                                                                                                                                                                                                                                                                                                                                                                                               |
| Secondary Objectives                                                                                                                                                                                                                                                         | Secondary Endpoints                                                                                                                                                                                                                                                                                                                                                                                                                                                                                                                                                                                                                                                                                                                                                                                                                      |

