### **4.5.1. Dose-Limiting Observation Period**

A minimum of 3 patients will be enrolled in each cohort, and the DLT observation period will be 14 days for each patient. Patients will continue to be monitored post-DLT period throughout the study. The totality of the safety data will be factored in by the SMC in the decision-making to move to enrollment of Cohort 2.

If a DLT occurs in 1 of the 3 patients during the DLT period, the cohort will be expanded to a total of 6 patients; if a DLT occurs in  $\geq 2$  patients in the total cohort of 6 patients, the MTD will be deemed to be exceeded, and that dose will not be escalated. The prior dose level will be evaluated to then proceed into the Expansion Cohort. The interval between patients in each cohort is at least 7 days with a 14-day interval between each cohort ([Section 4.4](#)).

The dose of agenT-797 will be escalated if none of the first 3 evaluable patients enrolled has a DLT based on SMC evaluations of data. If a cohort was expanded to include a total of 6 evaluable patients and no DLT occurs in the additional 3 patients, then the dose will be escalated based on the SMC evaluation of data.

After Amendment 7, the SMC will monitor safety on an ongoing basis.

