### 8.1.4. Dose-Limiting Toxicity Criteria

The DLT observation period is defined as 14 days after infusion of agenT-797. The nature, frequency, time to onset, severity of toxicities, medical history, and concomitant medication, as well as the success of standard medical management, will be analyzed to determine if a given toxicity should be considered a DLT by the SMC per charter.

A DLT is defined as any of the following at least possibly related AEs graded using NCI-CTCAE v5.0:

- General:
  - Any Grade 4 or 5 toxicity
- Hematologic:
  - Any Grade 3 hematologic toxicity that lasts for more than 7 days despite treatment

- Non-hematologic:
  - Any Grade 3 non-hematologic toxicity that lasts for more than 72 hours despite adequate treatment
  - Exceptions: Grade 3 events with a different definition of duration that are considered DLTs are the following:
    - Grade 3 renal or hepatic toxicity that lasts 7 days or longer
    - Any Grade 3 or higher toxicity that is cardiac, respiratory, or neurologic of any duration
- Immune:
  - Any Grade 2 acute GVHD that requires steroid therapy for > 7 days or that has progression of clinical signs and symptoms after 3 days of steroids or that has partial response after 14 days of treatment, or GVHD Grade 3 or higher
  - Any **new** Grade 3 CRS lasting more than 72 hours and/or **new** Grade 4 CRS of any duration at least possibly related to agenT-797. For patients presenting with Grade 2 or 3 CRS at baseline, worsening of baseline CRS grade, judged as at least possibly related to agenT-797, and occurring within 4 hours of infusion ([Lee 2019](#))
  - Any clinically significant Grade 3 autoimmune disorder that lasts for more than 72 hours at Grade 3 despite adequate treatment or any Grade 4 autoimmune disorder of any duration

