### **4.11.4 Adverse Events**

An AE is any untoward medical occurrence in a study subject administered an investigational medicinal product (IMP) which does not necessarily have a causal relationship with this treatment. An AE can therefore be any unfavorable and unintended sign (including a clinically significant abnormal laboratory finding), symptom, or disease temporally associated with the use of an IMP, whether or not considered related to the IMP. Adverse events may include the onset of new illness and the exacerbation of pre-existing conditions.

Other untoward events occurring in the framework of a clinical study will be recorded as AEs, e.g. those occurring during treatment-free periods (including screening or post-treatment follow-up periods), in association with study-related procedures and assessments.

Concomitant illnesses, which existed before entry into the clinical study, will not be considered AEs unless they worsen during the treatment period. Pre-existing conditions will be recorded as part of the subject's medical history.

A treatment-emergent adverse event (TEAE) is defined as an AE that begins or that worsens in severity after at least one dose of the study drug has been administered.

Any AEs with incomplete start and end dates/times will be treated as follows:

Adverse events with unknown start and/or end times (but where the date is known) will be imputed with a time of 00:00 h for the tabulations but will be shown as NK: NK in the listings (where NK = Not Known).

Adverse events with completely unknown start dates will be considered as treatment-emergent for the tabulations and will be shown as NK in the listings. Partially complete AE dates will not be imputed in the listings and the available day, month and year components will be used to determine if an adverse event is treatment-emergent taking the first dosing date and end of study date as references.

Adverse events will be coded using the MedDRA version 22.0 or higher.

The relationship or association of the study medication in causing or contributing to the AE will be characterized by the Investigator using the following classification and criteria:

- Possibly or probably related: A clinical event, including laboratory test abnormality, with a reasonable time sequence to study medication administration that might or might not be also explained by concurrent disease or other drugs or chemicals.

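### The protocol exempts anticipated disease deterioration from the AE definition with no exception for possibly drug-related events, so such respiratory worsening can be left out of the DLT count and the primary endpoint

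*Combined protocol and SAP*

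**What the plan says.** Protocol 8.1.1 gives the usual ICH definition of an AE and then a list with two exemptions. Events of the infection that are "captured in the study as a clinical activity measure, which does not need to be recorded as an AE" form the first. Worsening of the trial disease is the second, "which should not be regarded as an AE as far as the deterioration can be anticipated". Neither mentions events that may be related to agenT-797.

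Protocol 8.1.4 builds DLTs on AEs: "A DLT is defined as any of the following at least possibly related AEs graded using NCI-CTCAE v5.0". One limb is "Any Grade 3 or higher toxicity that is cardiac, respiratory, or neurologic of any duration". The window is fixed: "The DLT observation period is defined as 14 days after infusion of agenT-797".

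Protocol 8.1.7 has the investigator judge relationship for AEs. The primary endpoint in protocol section 3 is "Number and severity of adverse events (AEs) and dose-limiting toxicities (DLTs) at evaluated dose levels".

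SAP 4.11.4 has its own AE definition. It contains neither exemption and says: "Adverse events may include the onset of new illness and the exacerbation of pre-existing conditions".

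**The concern.** The trial enrols patients with moderate to severe ARDS, so the lung is both the diseased organ and an organ in which toxicity would matter. Respiratory worsening after the infusion could come from the disease, from the cells, or from both. Under 8.1.1 an investigator who regards it as anticipated need not record an AE. Without an AE, 8.1.7 does not ask for a causality judgement, and the 8.1.4 definition is not met. The question of whether the event was expected is in effect settled before the question of whether it was related.

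The clinical-activity exemption reaches the same ground. Intubation, mechanical ventilation and oxygenation support are efficacy parameters in protocol 4.16.6. The SAP reports them as median times, not as graded events with a causality assessment.

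The trial is open-label with one arm, so these judgements are unblinded and no concurrent control would show a shortfall in recorded events. At stake are the primary endpoint and, in Part 1, the count that drove dose escalation. The SAP cannot recover events that sites never entered.

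**Working it through.** The documents give no figure to reproduce. The claim rests on the text, and the arithmetic only illustrates what it could mean.

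**Text, step by step**

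1. 8.1.1: anticipated worsening of the disease is not an AE, and infection events captured as clinical activity need not be recorded as AEs. No exception for possible drug-relatedness.
2. 8.1.7: relationship is assessed for AEs.
3. 8.1.4: every DLT limb, including the respiratory one, requires an at least possibly related AE.
4. Section 3: AEs and DLTs are the primary endpoint.
5. SAP 4.11.4: no exemption, so the definition behind the tables is wider than the one governing data entry.

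**Illustration for Part 1**

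Protocol 4.5.1 escalates if none of the first three evaluable patients has a DLT. Otherwise: "If a DLT occurs in 1 of the 3 patients during the DLT period, the cohort will be expanded to a total of 6 patients". Escalation then requires no DLT in the additional three.

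Let *p* be the true probability that a patient has a DLT, *c* the share of DLTs left out as anticipated deterioration, and *q* = *p*(1 − *c*) the recorded rate. Patients are taken as independent. The documents give neither *p* nor *c*, so both are assumed over a range.

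P(escalate) = (1 − q)³ + 3q(1 − q)² × (1 − q)³ = (1 − q)³ + 3q(1 − q)⁵

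- *p* = 0.20, *c* = 0: 0.8³ + 0.6 × 0.8⁵ = 0.512 + 0.197 = 0.709
- *p* = 0.20, *c* = 0.5, so *q* = 0.10: 0.9³ + 0.3 × 0.9⁵ = 0.729 + 0.177 = 0.906
- *p* = 0.33, *c* = 0: 0.67³ + 0.99 × 0.67⁵ = 0.301 + 0.134 = 0.434 (before rounding the terms)
- *p* = 0.33, *c* = 0.5, so *q* = 0.165: 0.835³ + 0.495 × 0.835⁵ = 0.582 + 0.201 = 0.783

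| True DLT rate *p* | *c* = 0 | *c* = 25% | *c* = 50% | *c* = 75% |
|---|---|---|---|---|
| 20% | 70.9% | 81.4% | 90.6% | 97.3% |
| 33% | 43.4% | 60.5% | 78.3% | 93.3% |
| 40% | 30.9% | 49.4% | 70.9% | 90.6% |
| 50% | 17.2% | 35.1% | 60.0% | 86.2% |

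**Illustration for Cohort 4**

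Cohort 4 (up to 15 patients) has one dose and no escalation step, so the relevant quantity is what gets recorded.

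P(at least 2 recorded DLTs in 15) = 1 − (1 − q)¹⁵ − 15q(1 − q)¹⁴

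With half of DLTs left out, this falls from 83.3% to 45.1% at *p* = 0.20, and from 97.9% to 73.5% at *p* = 0.33.

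**The case against.** Exempting expected disease events is a legitimate convention in intensive care, and the protocol limits it to worsening that can be anticipated. Several provisions also work against omission:

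- 8.1.7 asks for a report when there is doubt whether something is an AE. It accepts possible relatedness even where concurrent disease could also explain the event. It also asks for relationship to both the agent and the underlying disease, which presupposes that some disease-attributable events are recorded.
- 8.1.3 requires CRS of Grade 2 or higher, and infusion reactions of Grade 2 or higher, to be reported as AESIs.
- 8.1.10 requires all deaths within 6 months to be reported.
- 8.1.4 leaves the DLT decision to the SMC under its charter, and 8.2 gives the SMC other clinical data as well as safety data.
- Ventilation, lung injury score, SOFA and blood gases are collected in any case.

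These points stand and lower the risk. They do not close the gap. The doubt clause does not help when the investigator has no doubt that the worsening was anticipated. Hypoxia counts towards a CRS grade only if no other cause explains it (Table 4 footnote). The stopping criterion for deaths in 4.5.3 leaves out those reported as due to the primary disease. SMC access to clinical data does not put an event into the AE or DLT tables.

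The safeguards do rule out three stronger readings. A reader might infer that an exempted event can never become a DLT; the doubt clause and the SMC's role leave routes open. A reader might infer that the reported rates are biased downward; the documents permit omission but do not show it. A reader might say that the SAP contradicts the protocol outright; its sentence on exacerbations is permissive, and the SAP omits the exemption without rejecting it.

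**Conclusion.** The concern holds as a gap in the definition. A stated rule, not a missing detail, allows possibly drug-related respiratory worsening to drop out of the respiratory DLT limb and the primary endpoint, and the SAP works from a different definition.

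The size cannot be determined from the documents. If half of DLTs were exempted, the chance of escalating would rise from 71% to 91% at a true rate of 20%, and from 43% to 78% at 33%. These figures rest wholly on the assumed rate and share. Only the direction does not: leaving out DLTs raises the chance of escalation and lowers the recorded count.

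A reader might instead compute the chance of two or more DLTs in six patients. That skips the first stage of the rule, where no DLT in three patients is enough to escalate, so it does not describe this design.

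Part 1 is marked as completed. For it, the point limits how the AE and DLT counts are interpreted and gives no ground for saying that an escalation decision was wrong. For Cohort 4 it affects what is collected.

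**What to change.** 1. Add one sentence to protocol 8.1.1: the exemptions do not apply to an event judged at least possibly related to agenT-797, or to one meeting AESI or DLT criteria. For this to work, relationship has to be judged before an event is exempted.
2. Use the same definition, exemptions and exceptions included, in SAP 4.11.4.
3. Tabulate disease-attributed respiratory deterioration on a separate line by cohort, whatever its AE status.

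Do not extend the exception to every event meeting SAE criteria. In ventilated ARDS patients, much expected worsening is life-threatening or prolongs the hospital stay, so that would largely undo the convention.

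The cost is some more AE entries, a slightly less favourable AE table, and an amendment with ethics committee approval (protocol 11.1). Cohort 4 counts may also not be directly comparable with those of Cohorts 1 to 3, recorded under the present wording, and the report should say so. The synopsis estimated that the last patient would complete in the second quarter of 2022, and the SAP took effect on 7 June 2022. If it is too late to change collection, the separate tabulation and a stated limitation on the AE and DLT counts can still be provided.
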